### Phase II Pilot Randomized Controlled Trials

#### Trial Design

In Phase II, we sought to conduct two 1-month pilot RCTs with patients recruited from primary care and ED settings. These trials sought to enroll approximately 60 participants each, who were randomized equally to receive either usual care or the BPMED intervention (see Figure 1 for participant flow through the trials). We chose these specific settings to reflect the way patients in our community engage with the health care system and to assess potential scalability of our intervention to real world clinical practice. Although Whittaker et al advocates the use of non-randomized pilot tests in the development and evaluation of mHealth interventions [14], we chose to use an RCT design of BPMED compared to usual care control so that we may be able to determine potential intervention effects on primary and secondary outcome measures at 1-month follow-up.

**Figure 1 figure1:**
[figure not shown]
Participant flow through BPMED trials.

#### Human Subjects Protections

The methods utilized in the two pilot RCTs were approved by the Wayne State University Institutional Review Board (#0410810B3E).

#### Participant Recruitment

To enlist participants for the primary care pilot RCT, a combination of recruitment methods were used including targeted recruitment letters mailed directly to potentially eligible participants who met clinical eligibility requirements as identified through retrospective records analysis of electronic medical records, recruitment posters displayed in primary care clinic exam rooms, and direct provider referral. Interested, potentially eligible participants were screened via phone, and those who met inclusion criteria were scheduled for a baseline data collection visit. Potential participants who previously participated in the Phase I focus groups were not excluded from participation in the pilot RCTs. To recruit participants for the ED pilot RCT, patients meeting clinical eligibility criteria were identified initially through real-time monitoring of the ED tracking board by trained research assistants. Recruitment, screening, and enrollment were conducted onsite in the Detroit Receiving Hospital ED and typically occurred directly after patient discharge from the ED.

#### Inclusion/Exclusion Criteria

To be eligible to participate, participants were required to self-identify as African American, be at least 18 years of age, have a diagnosis of HTN based on ICD-9 codes documented in the medical record, own a mobile phone capable of receiving and sending text messages, and be English speaking. Additional inclusion criteria specific to the primary care pilot included having uncontrolled HTN on two successive clinic visits prior to screening (clinic SBP >140 mm Hg, DBP >90 mm Hg or SBP >130, DBP >80 for those with diabetes or kidney disease) as documented in the medical record, and be taking at least one antihypertensive medication. Additional inclusion criteria specific to the ED pilot included having elevated blood pressure on successive measurements. Exclusion criteria included reporting strict adherence to medication regimens, receiving hemodialysis, plans to move >50 miles from the recruitment site within the next 3 months, diagnosis of resistant HTN documented in the medical record, plans to terminate mobile phone contract during the next month, compliance risk, and/or other major health problems that would make participation in this study difficult.

#### Intervention

All trial participants were fully informed about the risks and benefits of participating in this study, and written informed consent was obtained from all participants. Prior to randomization, all participants completed a baseline survey assessing demographics, mobile phone use, medication adherence, and medication adherence self-efficacy, as well as having their blood pressure taken. Primary care patients had been previously instructed to bring all antihypertensive medications with them to the baseline data collection visit so that pill counts could be taken to be used as an additional measure of medication adherence. In the ED trial, given that many participants were not currently taking medications to treat their HTN, all ED trial participants were given a 35-day supply of an appropriate antihypertensive medication. After completing all baseline measures, participants were block-randomized with a 1:1 ratio to either the usual care control or BPMED intervention group. Intervention group participants were then enrolled in BPMED and trained on how to use the program. All participants, regardless of trial assignment, were asked to come back for a 1-month follow-up visit where medication adherence, medication adherence self-efficacy, and blood pressure measures were assessed. In addition, intervention group participants completed a brief BPMED satisfaction questionnaire and open-ended interview at 1-month follow-up. This qualitative follow-up among intervention group participants post trial is advocated by Whittaker et al in the development and evaluation of mHealth interventions [14]. All participants received US $25 at the conclusion of baseline and 1-month follow-up data collection visits, for a possible total of US $50/participant. Any participant who indicated that text messaging was not included in their mobile phone plan was reimbursed US $0.20/text message sent or received as a part of their participation in this study. Finally, parking expenses were covered for primary care trial participants.

#### Outcomes

Medication adherence was the primary outcome of interest in this study and was measured using the MMAS [15], pill counts, and an additional self-report of medication adherence. For the primary care trial, medication adherence change from baseline to 1-month follow-up was of particular interest. In the ED pilot, adherence at follow-up was the primary outcome of interest due to the fact that some participants were not taking an antihypertensive medication at baseline. Secondary outcome measures of interest included medication adherence self-efficacy as measured by the Medication Adherence Self-Efficacy Scale [16], blood pressure, and participant satisfaction with BPMED. We also conducted post-trial qualitative interviews and questionnaires to assess BPMED participant perceptions of the program. In addition to participant outcomes, logs of unintended system down time will be analyzed to understand whether participant reminders were sent as expected.

#### Trial Statistical Methods

Descriptive statistics will be used to describe participant characteristics and intervention satisfaction at follow-up. Categorical data will be displayed as frequency and percentages, and where appropriate, chi-square tests will be used for comparison. Continuous variables such as medication adherence, medication adherence self-efficacy, and blood pressure will be expressed as mean (standard deviation), and means will be compared using two-tailed unpaired independent samples *t* tests. Regression models, controlling for variables such as gender, age, and other potentially important confounders, will be used to predict improvements in primary and secondary outcomes. All statistical analysis will be carried out using STATA version 12.0.

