### Hypotheses

In our Phase II primary care pilot RCT, we hypothesize that individuals assigned to the text message intervention will have (1) a greater increase in medication adherence from baseline to 1-month follow-up as compared to individuals receiving usual care treatment, (2) a greater increase in medication adherence self-efficacy from baseline to 1-month follow-up as compared to individuals receiving usual care treatment, and (3) a greater reduction in systolic and diastolic blood pressure (SBP and DBP) from baseline to 1-month follow-up as compared to individuals receiving usual care treatment.

Because it is expected that not all participants in the ED pilot RCT will be undergoing active treatment for HTN at the time of enrollment, Hypotheses #1 and #2 will not be as salient in the ED trial due to lack of meaningful baseline adherence and medication self-efficacy measures.

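### The stated between-arm comparison is an unadjusted t test and no stated model names the baseline value of the outcome, so precision is given up in primary care and for ED blood pressure

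*Protocol article*

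**What the plan says.** Trial Statistical Methods in the protocol article treats adherence, self-efficacy and blood pressure as continuous and says that "means will be compared using two-tailed unpaired independent samples" t tests. It adds regression models "controlling for variables such as gender, age, and other potentially important confounders", which "will be used to predict improvements in primary and secondary outcomes". The baseline value of the outcome is named in neither sentence.

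The form of the outcome differs by trial. Under Outcomes: "For the primary care trial, medication adherence change from baseline to 1-month follow-up was of particular interest". The primary care hypotheses are also worded as change, for example "a greater reduction in systolic and diastolic blood pressure (SBP and DBP) from baseline to 1-month follow-up". In the ED trial the primary outcome is adherence at follow-up, because some participants were not on treatment at baseline.

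The baseline data exist. Under Intervention: "Prior to randomization, all participants completed a baseline survey assessing demographics, mobile phone use, medication adherence, and medication adherence self-efficacy". The same sentence says that blood pressure was taken then too. Each trial aimed for about 60 participants allocated 1:1, so about 30 per arm.

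**The concern.** With about 30 per arm, the width of the confidence interval decides how much either pilot can say about effect, and the article itself lists small samples as a limitation. A baseline measurement of the same outcome is often the strongest predictor of its follow-up value.

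A follow-up-only t test does not use it. A change-score t test uses it with a fixed slope of 1, which is generally not the slope that minimizes variance. A model that estimates the slope uses data already held and needs no further participants. What is at stake is interval width and power, not the validity of the comparison.

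**Working it through.** **Inputs from the article.** 30 per arm (about 60 per trial, 1:1); two-sided comparison; baseline adherence, self-efficacy and blood pressure collected before randomization. The article gives no SD, no baseline-to-follow-up correlation, no effect size and no sample size derivation, so there is no planned figure to reproduce.

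**Assumptions.** No dropout; correlation r from 0.3 to 0.8; k = baseline SD / follow-up SD, first set to 1. Variances are in units of the follow-up variance.

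**Formulas.**
- Follow-up only: 1
- Change score: 1 + k² − 2rk, which is 2(1 − r) when k = 1
- ANCOVA: 1 − r²

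Change minus ANCOVA is (k − r)², and follow-up-only minus ANCOVA is r². Neither can be negative. So, apart from the degree of freedom spent on the slope, ANCOVA cannot be less precise than either alternative, whatever r and k are.

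**Results for k = 1.** The ANCOVA/change ratio is (1 + r)/2; for r = 0.3, 0.91/1.40 = 0.65.

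| r | Change | Follow-up only | ANCOVA | ANCOVA/change | ANCOVA/follow-up only |
|---|---|---|---|---|---|
| 0.3 | 1.40 | 1.00 | 0.91 | 0.65 | 0.91 |
| 0.5 | 1.00 | 1.00 | 0.75 | 0.75 | 0.75 |
| 0.7 | 0.60 | 1.00 | 0.51 | 0.85 | 0.51 |
| 0.8 | 0.40 | 1.00 | 0.36 | 0.90 | 0.36 |

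**As equivalent sample size.** ANCOVA on 60 participants matches a change-score t test on 60 × 1.40/0.91 = 92 (r = 0.3), 80 (0.5), 71 (0.7) or 67 (0.8). Against follow-up only it matches 60/0.91 = 66, then 80, 118 and 167.

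**As interval half-width** (1.96 × √(2/30) × √variance, in follow-up SDs). Follow-up only gives 0.51 throughout. Change versus ANCOVA gives 0.60 versus 0.48 (r = 0.3), 0.51 versus 0.44 (0.5), 0.39 versus 0.36 (0.7) and 0.32 versus 0.30 (0.8).

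**Sensitivity to k.** With an assumed k = 0.7 the change-score variance is 1.49 − 1.4r.

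| r | Change | ANCOVA | Cut versus change | Cut if k = 1 |
|---|---|---|---|---|
| 0.3 | 1.07 | 0.91 | 15% | 35% |
| 0.5 | 0.79 | 0.75 | 5% | 25% |
| 0.7 | 0.51 | 0.51 | 0% | 15% |

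The gain over change scores therefore depends strongly on k and vanishes when k = r. The gain over follow-up only depends on r alone.

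A change score is less precise than ignoring baseline when r < k/2, that is r < 0.5 for k = 1 and r < 0.35 for k = 0.7.

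**The case against.** **The covariate list is illustrative and the article is condensed.** Its wording does not exclude the baseline value, and a fuller protocol or analysis plan may name it. A reader might infer that the plan rules out baseline adjustment, or that an open covariate list is itself a fault. The article supports neither: the value is unnamed, not excluded, and the exact covariate set is commonly left to the fuller document. What stands is that the article does name its comparison, and the one it names is unadjusted.

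**The use of change scores in the t test is inferred.** Trial Statistical Methods does not say which means are compared. The reading comes from Hypotheses and Outcomes. It is the natural one, and a follow-up-only t test would also be no more precise than ANCOVA, apart from the degree of freedom.

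**The size is not known.** A reader might infer that r is low here, because eligibility requires uncontrolled pressure and excludes strict adherers, and hence that change scores do worse than ignoring baseline. No r is given. The primary care blood pressure criterion uses clinic visits before screening, not the study baseline reading. If eligibility did narrow the baseline range, k would fall as well and the gain over change scores could shrink. This objection limits the magnitude but not the direction.

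**The ED adherence outcome was chosen for a reason.** Hypotheses says that baseline adherence and self-efficacy are not meaningful in that trial, since not everyone is on treatment at enrollment. This stands in full: the figures above do not carry over to those two outcomes.

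**These are pilots.** Limitations puts feasibility and acceptability first and efficacy second, and no power target is set. That lowers the stakes. But the article chose a randomized design in order to look for effects, and a narrower interval serves that aim.

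**Conclusion.** The point holds as one of efficiency. For primary care outcomes measured at baseline and for ED systolic and diastolic pressure, the stated t tests give up precision that data already collected can supply. With k = 1 and r of 0.3 to 0.8, both assumed, ANCOVA variance is about 65% to 90% of the change-score variance and 91% to 36% of the follow-up-only variance. With a baseline SD 0.7 times the follow-up SD, the gain over change scores falls to between 15% and nothing for r of 0.3 to 0.7.

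A reader might infer that chance baseline imbalance biases the planned tests. It does not. At 30 per arm the standard error of the imbalance is √(2/30) = 0.26 SD, and at r = 0.5 (k = 1) an imbalance of that size would move an unadjusted estimate by about 0.13 SD. Randomization makes either direction equally likely, and the t test's standard error already reflects it. The t test stays valid, only less precise.

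No gain is claimed for ED adherence or self-efficacy, or for satisfaction, which has no baseline value.

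**What to change.** For each primary care outcome measured at baseline, and for ED systolic and diastolic pressure, state the main comparison as a linear model of the 1-month value on randomized arm plus the baseline value of the same outcome. Report the arm effect with a 95% CI and keep the t test as a supporting analysis. If change is preferred as the dependent variable, adding the baseline value as covariate gives the same arm effect.

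For ED adherence and self-efficacy, keep the follow-up comparison. Adjustment for antihypertensive use at baseline (yes/no) is optional and of uncertain gain.

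The cost is a few lines of text and one degree of freedom per model, with no new data for the main change. Data collection is already complete, so the change should be recorded with its date. Taking the baseline value of the same outcome as the covariate by rule leaves little room for choice after results are seen.

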## Results

Data collection from both pilots is now complete, and results from these pilots are expected to be published in early 2015.

## Discussion

### Principal Findings

This paper outlines the methodology of a two-phased study designed to develop (Phase I) and test (Phase II) the feasibility, acceptability, and preliminary efficacy of text message medication reminders to improve medication adherence in African Americans with uncontrolled HTN. Through the completion of the two pilot RCTs, we seek to add to the growing evidence base of mobile phone–based mHealth approaches for chronic disease self-management. With a rigorous study design, we hope to advance the field of mHealth beyond single group quasi-experimental research designs. Moreover, we hope to demonstrate the feasibility and acceptability of our approach among an urban African American population that suffers from considerable HTN-related health disparities and is often overlooked as a good candidate for technology-based behavior change interventions.

### Limitations

Perhaps the largest limitation to this study is our reliance on a short-term 1-month follow-up. This 1-month follow-up period was chosen for several reasons. First of all, this study was designed as a pilot project and was primarily concerned with showing feasibility and acceptability of our approach, with secondary emphasis on demonstrating preliminary efficacy. In addition, our 1-month follow-up period was chosen out of an initial concern of the stability of mobile phone numbers in this population.

Another limitation to our approach is our dependence on small sample sizes. To address this, depending on the differences in results of our two pilots, we will consider pooling the results if appropriate. We also acknowledge a lack of health care provider feedback in the design of BPMED and that many members of the care team, including physicians, nurses, and pharmacists, may have valuable insight to provide in the development of this sort of intervention. Given that this is a consumer-facing intervention that could be used independent of an established patient-provider relationship, we made the conscious decision to focus exclusively on the patient perspective in our design, but we do understand that additional provider feedback from a variety of care team members may have improved our ultimate design.

Finally, the lack of additional rigorous objective measures of medication adherence, such as the use of electronic pill bottles or other objective devices, may weaken our primary outcome measure. The decision not to use such devices was made out of budgetary necessity. Future work should seek to use more rigorous measures of medication adherence.

### Comparison With Prior Work

The evidence supporting long-term efficacy of text message medication reminders is largely missing from the literature [11], and the evidence supporting short-term efficacy has been mixed. Improvements in medication adherence as a result of receiving text message reminders have been demonstrated for adherence to antiretroviral therapy (ART) for people living with HIV/AIDs [17], as well unspecified medication regimens [18], and a variety of conditions and treatments, including type 2 diabetes [19], glaucoma [20], schizophrenia [21], and asthma [22]. However, other studies focused on text message reminders for acne medications [23] and oral contraceptives [24] have found no effect. A recent systematic review of text message reminders for health services by Kannisto et al [25] identified 60 studies that met inclusion criteria. Of those, 63% were focused on studies that utilized text message reminders for medication or treatment, whereas the other 37% were focused on clinical appointment reminders. Kannisto et al report that 77% of studies report improved outcomes on primary outcome measures of interest. Despite largely positive data suggesting the efficacy of the use of text message reminders for health care services, the authors acknowledge that more well-conducted studies are still needed to build the evidence base for this approach [25].

Although several studies have investigated the use of text message medication reminders for a variety of diseases, conditions, and therapeutic regimens, little work has been done to study this approach within the context of HTN. Moreover, few studies have been published to date that focus on the use of this approach within an urban, African American population. This trial protocol marks one of the first RCTs testing the efficacy of text message medication reminders on medication adherence among hypertensive African American participants.

### Conclusions

This study was designed to determine preliminary feasibility and acceptability of our approach in a cohort of African Americans with uncontrolled HTN in primary care and ED settings. Through our 1-month pilot RCTs, we also expect to demonstrate preliminary efficacy of BPMED to provide support for further exploration of the use of text message medication reminders to improve HTN-related outcomes in underserved urban minorities.

## Abbreviations

ART: antiretroviral therapy
CUS: Center for Urban Studies
DBP: diastolic blood pressure
ED: emergency department
HTN: hypertension
ICD-9: International Classification of Diseases version 9
mHealth: mobile health
MMAS: Morisky Medication Adherence Scale
RCT: randomized controlled trial
SBP: systolic blood pressure
WSU: Wayne State University
